##### Analyses of primary outcome

The rates of RFS will be estimated using the Kaplan–Meier method and will be compared between two intervention groups using two-sample log-rank tests. A univariable Cox proportional hazards regression will be conducted to estimate the hazard ratio for recurrence in TIVA versus GAS groups. As this is a large, randomized trial, we expect that enough number of subjects can be accrued without severe unbalance in each level of major confounding factors such as cancer stage. Multivariable analyses will be further performed to account for possible confounding because they usually can increase the precision of the estimated treatment effect and thus add power to the trial (Canner 1991). In the multivariable Cox proportional hazards regression model, the treatment effect will be estimated after adjusting these confounding factors: center, age, sex, ethnic origin, type of surgery, cancer stage, cell type, tumor size, resection margin, invasion of vascular/lymphatic/perineural/visceral pleura, tumor necrosis, pre-and postoperative adjuvant treatment, major gene mutation status, amount of intraoperative opioids, use of regional analgesia and some covariates with *p* value less than 0.1 in the univariable model (Maher et al. 2014; Sessler et al. 2019). Adjusted survival curves will be drawn to present survival probabilities estimated by univariable or multivariable Cox regression models.

Anticipating a potential difference in postoperative care between centers, we expect that there would be a difference in treatment effect (i.e., the hazard ratio for recurrence in the TIVA group versus the GAS group) between centers. Therefore, a stratified analysis or a clustered analysis will be performed to account for the between-center difference. The violation of the proportional hazards assumption will be visually inspected by Schoenfeld residual plots. If there is a severe violation of the proportional hazards assumption, various advanced methods such as accounting for time-varying confounder or time-dependent effects will be adopted. If a sample size allows, we will conduct subgroup analyses, in which subgroups are constructed according to each cancer type, cancer stage, age group, and sex. These analyses may help identify specific subgroups of patients for whom the intervention appears especially helpful or not helpful. For sensitivity analysis, Fine and Gray’s test will be used to compare cumulative incidence curves for RFS if competing risks due to non-cancer deaths exist.

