### Randomization

A stratified block randomization with a block size of 4 will be used to allocate subjects into two intervention groups (TIVA and GAS) with a 1:1 ratio. A computer-generated assignment sequence will be stratified according to the participating site and clinical cancer stage, using a web-based automated randomization system (www.gastiva.org). This system is centralized, password-protected, and encrypted. At each participating site, random allocation will be done according to the assignment sequence before induction of anesthesia.

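### The primary log-rank test and Cox model ignore the randomisation strata; stratifying them by clinical stage and site group would gain about 2 to 6 points of power at no cost in patients

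*Protocol article*

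**What the plan says.** Under Randomization, the Protocol article specifies "A stratified block randomization with a block size of 4", and adds: "A computer-generated assignment sequence will be stratified according to the participating site and clinical cancer stage".

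Under Analyses of primary outcome, the Kaplan–Meier RFS rates "will be compared between two intervention groups using two-sample log-rank tests". The effect estimate follows: "A univariable Cox proportional hazards regression will be conducted to estimate the hazard ratio for recurrence in TIVA versus GAS groups". Neither step names a stratification factor. A multivariable Cox model is then added, in which "the treatment effect will be estimated after adjusting these confounding factors: center, age, sex, ethnic origin, type of surgery, cancer stage", along with pathology findings, resection margin, adjuvant treatment, opioid amount and covariates selected at p < 0.1.

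The same section turns to centres: "we expect that there would be a difference in treatment effect" between them, meaning in the hazard ratio itself. It concludes: "Therefore, a stratified analysis or a clustered analysis will be performed to account for the between-center difference". Stage is not part of that step.

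Sample-size calculations rests on an unadjusted Cox model with hazard ratio 0.83, 80% power and 4845 evaluable patients.

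**The concern.** Stage is strongly prognostic on the protocol's own figures: 10%, 20% and 35% recurrence for stages I, II and III in one cited source, and 13%, 35% and 60% in the other. When allocation is balanced within strata that predict outcome this well, an analysis that ignores them overstates the variance of the treatment comparison. The test becomes somewhat conservative, and the unstratified hazard ratio lies nearer to 1 than the within-stratum one. A trial sized at 80% power for a 3-point difference then gives up some of what its stratified randomisation could deliver.

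The centre step does not fill the gap. It leaves out stage. If it is a centre-stratified model with one common hazard ratio, it lets baseline hazards differ between centres but not the treatment effect, which is the stated reason for doing it.

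**Working it through.** **The plan's own figure.** With events per patient P = 0.20, 1:1 allocation and log hazard ratio B, N = (1.960 + 0.842)² / (P × 0.25 × B²) = 7.849 / (0.05 × B²).

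- B = 0.18 (ln 1.2 rounded): 7.849 / (0.05 × 0.0324) = 4845, the stated N. Expected events are 4845 × 0.20 = 969.
- B = ln 1.2 unrounded: 4723, within 3%.
- Dropout: 4845 / 0.9 = 5384, as stated.

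With the pooled event rate near 18.5% (20% in GAS, about 17% in TIVA), events are 4845 × 0.185 = 896, and Schoenfeld's formula gives 79.7% power at hazard ratio 0.83. This is the benchmark for the simulations.

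**Simulation.** From the protocol: N = 4845, blocks of 4 within site × stage, 3-year follow-up, two-sided 0.05, and the two sets of stage rates. Assumed:

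- stage mix 42/30/28 for the first source (0.42 × 10% + 0.30 × 20% + 0.28 × 35% = 20.0%) and 76/16/8 for the second (0.76 × 13% + 0.16 × 35% + 0.08 × 60% = 20.3%);
- exponential times, and a common within-stage hazard ratio;
- 22 sites with shares 40%, 30% and 20 × 1.5%, and site log-hazard SD 0.2.

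With 2,000 trials per setting, the Monte Carlo SE is about 1 point for power and 0.5 for type I error.

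| Log-rank test | Power, 10/20/35% | Power, 13/35/60% | Type I, 10/20/35% | Type I, 13/35/60% |
|---|---|---|---|---|
| Unstratified | 77.9% | 75.0% | 4.5% | 3.3% |
| By site | 78.1% | 74.9% | 4.4% | 3.3% |
| By stage | 79.4% | 79.4% | 5.0% | 4.1% |
| By site × stage | 79.8% | 79.5% | 5.1% | 4.4% |

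Full stratification gains 79.8 − 77.9 = 1.9 points and 79.5 − 75.0 = 4.5 points. Site alone recovers almost nothing. With a within-stage hazard ratio of 0.83, the unstratified estimate averages about 0.838 and 0.843.

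**Other runs.**

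- 13/35/60% with mix 78/13/9 (0.78 × 13% + 0.13 × 35% + 0.09 × 60% = 20.1%): about 76% unstratified against 81% by stage.
- Strata of stage × SMC/SNU/other: 73.4% against 78.7% with 13/35/60%, and 78.5% against 81.2% with 10/20/35%.
- A further run by stage and pooled site: gains of about 2 points (10/20/35%) and 5 to 6 points (13/35/60%).

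All point the same way, and pooling sites has no visible cost.

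**The centre step.** Let centre log hazard ratios vary around a mean of zero with SD 0.1 or 0.2 (assumed; 13/35/60% rates). The site-stratified log-rank then rejects 9.1% or 25.4% of the time, against 8.9% or 25.2% unstratified. Stratifying by centre makes no difference to effect variation.

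If the clustered option means a cluster-robust variance, and if 4:3:3 means two dominant sites plus 20 small ones (assumed), the effective number of clusters is 1 / (0.4² + 0.3² + 20 × 0.015²) = 1 / 0.2545 = 3.9. That is too few for such a variance to be reliable.

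**The case against.** **Stage and centre are adjusted for.** A reader might infer that they are ignored throughout. They are not: the multivariable Cox model names both. But that model is an additional analysis, conditions on post-randomisation variables such as resection margin, postoperative treatment and opioid amount, selects covariates by p value, and does not say whether its cancer stage is the clinical stage used for allocation. It does not replace a stratified primary test.

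**The unstratified hazard ratio is not biased.** Its shift towards 1 is mostly non-collapsibility: the marginal and within-stratum hazard ratios are different quantities. The sample-size section can be read as targeting the marginal one, since 20% against 17% gives ln 0.83 / ln 0.80 = 0.835. With the 13/35/60% rates and mix 78/13/9, a marginal hazard ratio of 0.83 needs about 0.817 within stage, and the unstratified test then has about 81% power; with exactly a 3-point reduction it has about 78%. So the documents do not support calling the design underpowered for its own target. Stratification would still add about 4 points in that scenario. This objection stands as a limit on the finding.

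**The gain may be smaller.** The protocol does not say whether its cited rates are by clinical or pathological stage. The lower type I figure, 4.5%, is not distinguishable from 5% given its Monte Carlo error.

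**The clustered option is undefined, and its detail may sit in the SAP.** A reader might infer that the plan permits a test with grossly inflated error. Type I error of about 14% does arise, but only for a cluster-robust variance under the assumed site split. The table footnote calls SMC, SNU and Others categories of sites, so two sites holding 70% is not established. A random treatment effect would be a clustered analysis that does address differing effects, so it is also too strong to say the centre step cannot do so.

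**Conclusion.** The point holds as a free improvement, not as an error that invalidates the analysis. The primary test and hazard ratio use neither randomisation factor. The test is valid and errs on the conservative side when the effect is common to all centres (type I error about 3.3% to 4.5%). The power forgone is about 2 points with the 10/20/35% rates and about 4 to 6 points with the 13/35/60% rates, nearly all of it due to stage.

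These sizes rest on the assumed stage mixes, a within-stage hazard ratio of 0.83, exponential times and the assumed site shares. They fall if clinical stage is a weaker predictor than the cited rates.

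The centre step omits stage and, in its common-hazard-ratio form, does not match its stated reason. Reliance on a cluster-robust variance would be unsafe if one or two sites hold most patients.

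**What to change.** - Make the primary test a log-rank stratified by clinical stage as used for randomisation and by pooled site group (SMC/SNU/other), with the hazard ratio from a Cox model with the same strata.
- Keep the unstratified log-rank and univariable Cox analyses as supportive.
- Assess differing centre effects by a treatment-by-site-group interaction or a random treatment effect by site, labelled supportive. Do not rely on a cluster-robust variance for inference.

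The cost is analysis wording, settled before group allocation is opened. No patients, data or change of sample size are needed. The reported hazard ratio becomes a within-stratum (conditional) one, which the text should state.

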##### Analyses of secondary outcomes

The LRFS, MFS, OS, and CSS will be analyzed using the same analytic methods as described for the primary outcome above. In addition, Gray’s test will be used to compare cumulative incidence curves for cancer-specific death if competing risks exist. For group comparison in the postoperative complication rate, the chi-square test or Fisher’s exact test will be used as appropriate.

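### Randomisation is stratified by site and clinical stage, but the first-listed primary test uses neither; naming a stratified analysis as primary would gain about 2 to 4.5 points of power at no cost

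*Protocol article*

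**What the plan says.** **Randomization section.** The design is "A stratified block randomization with a block size of 4", allocating to "two intervention groups (TIVA and GAS) with a 1:1 ratio", and "A computer-generated assignment sequence will be stratified according to the participating site and clinical cancer stage".

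**Analyses of primary outcome.** RFS "will be compared between two intervention groups using two-sample log-rank tests". For the estimate, "A univariable Cox proportional hazards regression will be conducted to estimate the hazard ratio for recurrence in TIVA versus GAS groups". No strata are named for either. Two further analyses follow:
- In a multivariable Cox model, "the treatment effect will be estimated after adjusting these confounding factors: center, age, sex, ethnic origin, type of surgery, cancer stage" and many more. The stated reason is a gain in precision and power.
- For centres, "a stratified analysis or a clustered analysis will be performed to account for the between-center difference".

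**Analyses of secondary outcomes.** Locoregional RFS (LRFS), metastasis-free survival (MFS), overall survival (OS) and cancer-specific survival (CSS) use the same methods as RFS.

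**Sample-size calculations.** The trial is sized with a Cox regression on anaesthesia group without covariate adjustment (R² = 0% in the notes to Table 2). The title of Table 2 names two-sided log-rank tests.

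**The concern.** Stage is strongly prognostic on the protocol's own figures: 3-year recurrence for stages I, II and III is 10%, 20% and 35% in one cited source and 13%, 35% and 60% in the other. Stratified blocks of 4 keep the arms nearly balanced on stage, so between-stage differences add little to the chance variation of the treatment comparison. An unstratified log-rank test computes its standard error as if that variation were still present. The result is a test run below its nominal 5% that forgoes power the randomisation has already secured.

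The article also leaves open which analysis counts. A log-rank test, a univariable Cox model, a multivariable Cox model and a stratified or clustered analysis are all planned, and they could disagree. None of them is a clean analysis by the two randomisation factors:
- The multivariable model says cancer stage, not clinical stage as randomised, although Table 1 collects both clinical and pathological stage. It also adjusts for variables that arise after randomisation (amount of intraoperative opioid, postoperative adjuvant treatment) and adds covariates selected at p < 0.1.
- The centre analysis leaves out stage and does not fix its method or role.

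**Working it through.** **1. The plan's own figure.** Schoenfeld's formula with 1:1 allocation is d = 4(z₀.₉₇₅ + z₀.₈₀)² / (ln HR)². With ln HR = −0.18 (HR 0.835), d = 4 × 7.849 / 0.0324 = 969 events. Dividing by the 20% event rate gives 969 / 0.20 = 4845. Allowing for 10% dropout gives 4845 / 0.90 = 5383.3, rounded up to 5384. Both stated numbers reproduce, and the calculation contains no stratification.

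**2. Simulation inputs.**
- From the protocol: 4845 patients, 22 sites shared 4:3:3 (40%, 30%, and 20 sites at 1.5% each), blocks of 4 within site by stage, 3 years of follow-up, two-sided 5%, and the two sets of stage-specific rates.
- Assumed: exponential times, and the stage mix, which the article does not give. Each mix was chosen to give about 20% control recurrence. For example, 0.80 × 13% + 0.10 × 35% + 0.10 × 60% = 19.9%, and 0.40 × 10% + 0.35 × 20% + 0.25 × 35% = 19.75%.
- The article does not say whether 0.83 is the marginal or the within-stratum HR, so both readings were run.

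**3. Results, unstratified versus stratified log-rank test.**

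| Stage rates; assumed mix I/II/III | 0.83 read as | Type I error | Power |
|---|---|---|---|
| 13/35/60%; 80/10/10 | marginal (within-stratum 0.816) | 3.6% vs about 5.4–5.6% | 80.8% vs 85.3% |
| 10/20/35%; 40/30/30 | marginal (within-stratum 0.825) | 4.9% vs about 5.5% | 81.3% vs 83.2–83.6% |
| 13/35/60%; 76/17/7 | within-stratum | 3.8–4.0% vs 5.2–5.3% | 74.1–75.3% vs 78.1–79.7% |
| 10/20/35%; 40/35/25 | within-stratum | 4.4% vs 5.1% | 77.0–77.7% vs 79.0–79.9% |

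Rows 1 and 2 use 5000 trials per cell (Monte Carlo standard error 0.3 points for type I error), and the stratified figures cover stage alone and site by stage. Rows 3 and 4 use 10,500 trials per cell (0.2 points for type I error, 0.4 for power), stratify by site by stage, and span an assumed between-site SD of the log hazard from 0 to 0.3. A smaller repeat run (1500 per cell) gave unstratified type I errors of 3.3% and 4.6% and a gain of about 1.5 to 5 points.

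The gain is about 4 to 4.5 points with the 13/35/60% rates and about 2 points with the 10/20/35% rates.

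**4. Which factor matters.** In the within-stratum runs, stratifying by stage alone gives 78.8–79.8% power (13/35/60%) and 79.2–79.6% (10/20/35%), nearly the whole gain. Stratifying by site alone changes power by less than 0.5 point. Using the full site-by-stage strata costs almost nothing compared with stage alone.

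**5. Where the gain comes from (row 1).** The mean model standard error of the log HR is 0.0674 unstratified, 0.0674 by stage and 0.0678 by site and stage, so the interval does not narrow. The true sampling SD of the unstratified log HR is about 0.063, a ratio of 0.063 / 0.0674 = 0.935.
- Type I error: P(|Z| > 1.96 / 0.935 = 2.10) ≈ 3.6%, as simulated.
- Unstratified power: the mean HR is 0.829, so 0.1875 / 0.0674 = 2.78 and Φ((2.78 − 1.96) / 0.935) ≈ 81%.
- Stratified power: the mean HR is 0.815, so 0.2046 / 0.0678 = 3.02 and Φ(3.02 − 1.96) ≈ 85.5%.

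The stratified analysis estimates a conditional HR that lies further from 1, with a standard error that matches the design.

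**The case against.** The case for leaving the plan alone has several sound parts.

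- *The log-rank test is not declared decisive.* This stands: the role is an inference from its place in the text, the title of Table 2 and the unadjusted sample size. If the inference is rejected, the lack of a named confirmatory analysis remains. The analysis plan that the article mentions may rank the analyses, but the choice of test is stated here and sets the expectation.
- *The plan does not ignore the two factors.* This also stands for the plan as a whole, since the multivariable model includes centre and stage and a centre analysis is promised. Neither is a clean analysis by the factors as randomised.
- *Test and sample size agree, and the planned power is met.* This stands if 0.83 is the marginal HR (80.8% and 81.3%). A reader might infer from the lower rows of the table that the trial is underpowered. That follows only if 0.83 is the within-stratum HR, which the article does not say.
- *The rates may not describe clinical stage.* The article does not say whether they are by clinical or pathological stage, and eligibility stops at clinical stage IIIA while the rates are for stage III. If clinical stage separates risk less well, the gain shrinks.

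A reader might also infer that the confidence interval is needlessly wide, or that the unadjusted HR is biased toward 1. Neither follows. The model standard error is about 0.067 either way, and the shift in the HR is non-collapsibility: marginal and conditional HRs are different quantities.

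**Conclusion.** The point holds as a matter of efficiency and specification. The first-listed RFS test omits the randomisation factors, and no analysis is named as confirmatory. The unstratified test is conservative, with type I error of about 3.3% to 4.9%, and gives up about 2 to 4.5 points of power, nearly all because of stage. A reader might take a test that misses its nominal level to be invalid. It is not, because the departure is downward and false positives are not inflated.

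The size of the gain rests on assumed stage mixes, on exponential times, and on the quoted rates applying to clinical stage. Its direction is the same in every scenario examined and under both readings of 0.83. No calculation was made for postoperative complications, so no claim is made about that comparison.

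**What to change.** - Name one primary RFS analysis: a log-rank test stratified by clinical stage as entered at randomisation and by site, with small sites pooled by a rule fixed in advance. Take the HR from a Cox model stratified by the same factors and describe it as a conditional HR.
- Apply the same to LRFS, MFS, OS and CSS.
- Keep the unstratified log-rank test, the univariable Cox model and the multivariable Cox model as supportive, and say so.
- State in the sample-size section whether 0.83 is a marginal or a within-stratum HR. On the simulations above, the stratified test has about 83% to 85% power in the first case and about 78% to 80% in the second.

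The cost is wording in the protocol and analysis plan. Both factors are already held in the randomisation system, and no patients or data items are added.

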### Protocol

The TIVA group will receive propofol for both induction and maintenance of general anesthesia. The GAS group will receive one or more volatile anesthetics (sevoflurane, desflurane, or isoflurane) for induction and maintenance of anesthesia during the surgery. For the GAS group, propofol, midazolam, remimazolam, etomidate, or ketamine can be used with inhalation agents as co-induction agents at the discretion of the attending anesthesiologist. There are no protocol-specific restrictions for concurrent medication in this pragmatic study. In both groups, adjuvant drugs, such as opioids, ketamine, lidocaine, dexmedetomidine, and neuromuscular blocking agents will be administered according to standard institutional procedures at each site, as is postoperative analgesia including neuraxial or regional blocks.

All participating patients, regardless of the study arm into which they are randomized, will be monitored and managed following general standard-of-care practices aimed at maintaining optimal conditions. Both intraoperative and postoperative management (unrelated to anesthetic management) will be decided by the attending physicians, following the established protocols at each center. However, in order to ensure a high standard of anesthetic management, several common strategies have been established: before surgery, the surgical procedure (video- or robot-assisted thoracic surgery or thoracotomy) will be chosen by the attending thoracic surgeon at each center based on clinical features including patient age, comorbid disease, pulmonary function, and tumor characteristics. Appropriate antibiotic prophylaxis will be administered, and standard pharmacological prevention of postoperative nausea and vomiting will be utilized per institutional practice.

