### Statistics

#### Sample-size calculations

Sample size was calculated based on RFS, the primary outcome of the trial. We expect an overall 3-year recurrence rate of 20% in GAS group based on previous studies (Taylor et al. 2012) [*N* = 1143, event rate of 10%, 20%, and 35% for Stage I, II, III, respectively] and Yun et al. (Yun et al. 2022) [*N* = 6012, event rate of 13%, 35%, and 60% for Stage I, II, III, respectively]). A Cox regression on the anesthesia group (TIVA group versus GAS group) with a sample size of 4845 observations achieves 80% power at a 0.05 significance level to detect a hazard ratio of 0.83 in the TIVA group compared to the GAS group. This HR corresponds to an absolute risk reduction of 3% in the TIVA group compared to the GAS group. Since the most important predictors of NSCLC survival are patient-related factors and aggravating tumor characteristics (Enlund et al. 2023), we expect only a 3% difference related to the anesthetic regimens. Although a 3% absolute difference between study groups is small, we believe it is clinically significant given the ease and low cost of the anesthetic interventions. Anticipating a 10% dropout rate, 5384 subjects should be enrolled to obtain a final sample size of 4845 subjects (in each group, 2692 subjects) (Table 2). No adjustment is made on other covariates in Cox regression, under the assumption that there is no collinearity between the anesthesia group and covariates. As no study has yet examined the effect of the TIVA group compared to the GAS group on RFS, we assumed a conservative condition for the correlation structure which leads to maximizing the estimated sample size. Although we will be conducting competitive enrollment, we expect a total of 5384 subjects to be enrolled in SMC:SNU: Other in a ratio of 4:3:3 (SMC; Samsung Medical Center, SNU; Seoul National University).

**Table 2 Tab2:** The estimated study power using two-sided log-rank tests at a significance level of 0.05 according to different assumed 3-year RFS rates at each arm

Scenario	Hazard ratio	1/hazard ratio	Risk reduction	*N*	*N***	*N* per group			
						Total	SMC	SNU	Others
1	0.65	1.54	5%	1132	1260	630	315	126	63
2	0.73	1.37	5%	1533	1704	852	427	170	85
3	0.78	1.29	5%	2010	2236	1118	559	224	111
4	0.81	1.24	5%	2374	2640	1320	660	264	132
5	0.83	1.2	2%	6460	7180	3590	1796	718	358
6	0.83	1.2	3%	4845	5384	2692	1348	538	268
7	0.83	1.2	4%	3876	4307	2154	1078	430	214
8	0.83	1.2	4%	3230	3592	1796	898	360	178

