##### Other details for analyses

All baseline variables will be descriptively compared between two intervention groups using appropriate summary statistics, such as mean and standard deviation, median and quartiles, or frequency and percent, and also proper testing methods, including two-sample *t*-test or Mann–Whitney test, chi-square test, and Fisher’s exact test. All tests will be two-tailed, and the statistical significance will be declared if *p* value < 0.05. All data analyses will be performed by a statistics analytic team using SPSS software (version 27.0; IBM Corp., Armonk, NY, USA) or R software (version 4.2.2; R Foundation for Statistical Computing, Vienna, Austria) or SAS software (version 9.4; SAS Institute, Cary, NC, USA) according to a pre-established statistical analysis plan.

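### The further multivariable Cox model for RFS adjusts for variables that arise after randomisation, so its treatment hazard ratio can be biased in either direction; the log-rank test and univariable hazard ratio are not affected

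*Protocol article*

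**What the plan says.** Under Randomization, allocation takes place before anaesthesia is induced. Under Analyses of primary outcome, recurrence-free survival (RFS) is compared by log-rank test, and a univariable Cox model gives the HR. The text then continues: "Multivariable analyses will be further performed to account for possible confounding because they usually can increase the precision of the estimated treatment effect". The adjustment list contains centre, demographic, surgical and pathological variables and also "pre-and postoperative adjuvant treatment, major gene mutation status, amount of intraoperative opioids, use of regional analgesia". It ends with an open set of further covariates chosen by univariable p<0.1.

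On how these variables come about, the Protocol section states: "In both groups, adjuvant drugs, such as opioids, ketamine, lidocaine, dexmedetomidine, and neuromuscular blocking agents will be administered according to standard institutional procedures". It treats postoperative analgesia, including neuraxial and regional blocks, in the same way, and later leaves opioids and adjuncts during maintenance to the anaesthesiologist. The Blinding section says that the attending anaesthesiologist cannot be blinded. Table 1 lists opioid use under operative data and adjuvant treatment under postoperative data.

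The section on secondary outcomes applies the same methods to locoregional RFS, metastasis-free survival, overall survival and cancer-specific survival.

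**The concern.** A confounder of a randomised comparison would have to influence allocation. A variable that comes into being after allocation cannot do that. It can be a mediator, meaning part of how the anaesthetic strategy acts, or a collider, meaning a joint result of the arm and of unmeasured patient risk. Adjusting for a mediator removes part of the effect the trial wants to measure. Adjusting for a collider creates an association between arm and outcome where there may be none.

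The article supplies the route from arm to covariate for opioids: unblinded staff choose them at their discretion. Regional analgesia follows institutional practice and clinician preference, and nothing says that the plan is fixed before allocation. Postoperative adjuvant treatment is also decided after allocation. Its link to the arm is less direct, for example through recovery from surgery.

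At stake is the credibility of the adjusted HR, which the article presents as the more precise estimate. The design effect is modest (HR 0.83), so a bias of a few hundredths matters. If the adjusted and unadjusted results disagree, the article has no stated rule for choosing between them.

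**Working it through.** **1. The sample size, to see whether it is touched.**

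Inputs from Sample-size calculations: "4845 observations achieves 80% power at a 0.05 significance level to detect a hazard ratio of 0.83" and "We expect an overall 3-year recurrence rate of 20% in GAS group". Tests are two-sided (Other details for analyses) and allocation is 1:1.

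- Events = (1.960 + 0.842)² / (0.25 × (ln HR)²).
- With |ln HR| rounded to 0.18 (ln 1.2 = 0.182): 7.849 / 0.0081 = 969 events.
- N = 969 / 0.20 = 4845, and 4845 / 0.9 = 5384 after rounding up.

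Both stated figures reproduce. The calculation assumes R² = 0 between arm and covariates. Randomisation justifies that for baseline covariates only.

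**2. Bias when there is no true effect and the covariate is a collider.**

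Assumed model, since the documents give no strengths: covariate M = a·arm + c·U + noise, with unit variance within arm. U is unmeasured risk with log-HR g per SD, and M has no effect of its own. Given M and arm, the expected value of U is c(M − a·arm), so the adjusted log-HR for the arm is approximately −a·c·g.

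The simulated values are Cox fits at n = 4845 with about 20% events and 300 runs per scenario.

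| Scenario | a, c, g | exp(−a·c·g) | Simulated adjusted HR | Unadjusted HR | Type I error, adjusted |
|---|---|---|---|---|---|
| Strong | 0.5, 0.5, 0.5 | exp(−0.125) = 0.88 | 0.89 | 1.00 | 41% |
| Strong, shift reversed | −0.5, 0.5, 0.5 | exp(+0.125) = 1.13 | 1.13 | 1.00 | 44% |
| Weak | 0.2, 0.3, 0.3 | exp(−0.018) = 0.98 | 0.98 | 1.00 | 7% |
| No shift | a = 0 | 1.00 | – | – | – |

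With 300 runs, the weak scenario's 7% cannot be told apart from 5%. Intermediate inputs give intermediate results: a = 0.5, c = 0.3, g = 0.5 gives exp(−0.075) = 0.93, and a = 0.3 with the same c and g gives exp(−0.045) = 0.96.

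**3. Loss of effect when the covariate is a mediator (true HR 0.83, arm shift 0.5 SD).**

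- Half of the effect runs through M: the direct part is exp(½ × ln 0.83) = 0.91. Simulated adjusted HR 0.91; the rejection rate falls from 81% to 28%.
- All of the effect runs through M: adjusted HR 1.00, rejection rate 7%.
- The arm does not affect M: unadjusted and adjusted HR are both 0.83, so there is no bias.

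**4. Loss of precision.**

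A 0.5 SD shift under 1:1 allocation gives R² = (0.25 × 0.5²) / (1 + 0.25 × 0.5²) = 0.0625 / 1.0625 = 0.059. At R² = 0.05 and 969 events, power is 78.0% instead of 80%; at R² = 0.10 it is 75.7%. This is small beside the possible bias.

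**5. Postoperative adjuvant treatment as a fixed covariate.**

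Time zero is surgery and treatment starts later. I simulated one million patients per scenario, with treatment given only to those event-free at 0.15, 0.25 or 0.5 years, uptake independent of or linked to unmeasured risk but not to the arm, and a true HR of 1 or 0.83. Adjustment moved the HR for the arm by less than 0.001 in every case. The coefficient of the inert adjuvant treatment was distorted: with uptake independent of risk it fell to about 0.91, 0.85 and 0.72–0.73.

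**The case against.** The strongest defence is that the multivariable model is not the main test. The log-rank test and univariable Cox model come first, the multivariable analyses are described as further work, Table 2 bases power on log-rank tests, and the sample size makes no covariate adjustment. This stands. A reader might infer that the primary analysis itself is biased or that the trial would be left without an answer. The documents do not support that, because the unadjusted comparison is planned and sound. What remains is that no sentence names it as decisive, while the article recommends the adjusted model for its precision and power.

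Other stronger readings also fail:

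- *The adjustment does bias the result.* It can. Bias requires the arm to shift the covariate, and the documents give no shift.
- *Immortal time biases the treatment effect.* It mainly distorts the adjuvant-therapy coefficient; the arm contrast did not move in the check above.
- *Resection margin belongs with opioids.* It is recorded after surgery, but surgeons are blinded behind opaque drapes, so an arm effect on it is weakly supported.
- *Missing mutation data would empty the model.* The documents give no figure for missingness, and its handling is commonly left to the statistical analysis plan.
- *The p<0.1 rule is itself a source of large bias.* No such effect was computed, and with about 969 events it is probably small. The rule does leave the model open until outcome data have been seen.

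**Conclusion.** The point holds for the further multivariable model for RFS and for the secondary survival outcomes that inherit it. Intraoperative opioid amount, regional analgesia and postoperative adjuvant treatment are wrongly classed as confounders, and conditioning on them can give a wrong adjusted HR. Under no true effect the bias is nil without an arm shift, and the adjusted HR runs from about 0.98 to about 0.89 or 1.13 over the assumed inputs. If the covariate carries half of a true 0.83 effect, the adjusted HR is about 0.91. All of these sizes rest on assumed covariate strengths. The case is clearest for opioids, where the article itself describes discretionary use by unblinded staff. The log-rank test, the univariable HR and the sample size are untouched. Severity: should-fix.

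**What to change.** 1. State that the log-rank test with the unadjusted HR decides the primary hypothesis, or name one baseline-adjusted HR instead.
2. Limit the adjusted model to a fixed list of pre-randomisation covariates already in Table 1, such as centre, clinical stage, age, sex, ECOG status and neoadjuvant therapy. Say that stage means clinical stage, since pathological stage is also collected.
3. Delete intraoperative opioids, regional analgesia, postoperative adjuvant treatment and the p<0.1 selection rule from that model.
4. Report the deleted variables by arm, or use them in an analysis labelled exploratory or mediation. Surgical pathology, including resection margin, may go in a sensitivity model.
5. Apply the same wording to the secondary survival outcomes.

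The cost is wording only. No new data are needed, and the numbers stay at 4845 evaluable and 5384 enrolled. The downside is that the adjusted model loses some prognostic covariates and the precision they might have added.
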